### Trial design {8}

This is a mechanistic, sham-controlled, randomized, parallel design, multi-site (2 sites), clinical trial in which participants with chronic SCI are assigned in equal ratios to one of three study groups (or arms). Group 1: Active transspinal stimulation while standing followed by locomotor training; Group 2: Active transspinal stimulation while lying supine followed by locomotor training; and Group 3: Sham transspinal stimulation while standing followed by locomotor training. Study outcomes are assessed for superiority before (baseline) and after 40 sessions of primed locomotor training.

## Methods: participants, interventions, and outcomes

### Study setting {9}

Neurophysiological assessments before and after 40 sessions of therapy are performed at the KLab4Recovery Research Program located at the College of Staten Island, City University of New York, New York, USA, an academic institution. Therapy and clinical assessments are performed at the KLab4Recovery Research Program and at one clinical research center (Spinal Cord Damage Research Center) of a government hospital (James J. Peters Veterans Affairs Medical Center, Bronx, New York USA). Both study sites are listed at ClinicalTrials.gov (https://clinicaltrials.gov/ct2/show/NCT04807764).

### Eligibility criteria {10}

The inclusion criteria for the participants are the following:

◦Willingness to comply with all study procedures and availability for the duration of the study.◦Ability to understand and sign informed consent.◦Male or female, age 18–70 years old.◦A diagnosis of first time SCI due to trauma, vascular or orthopedic pathology.◦At least 6 months after SCI.◦American Spinal Injury Association Impairment Scale (AIS) Grade C or D.◦Minimum bone mineral density − 2.49.◦Lesion at or above Thoracic 10 neurological level.◦Absent lower motor neuron injury.◦Presence of tendon reflexes.◦Stable medical condition without cardiopulmonary disease or cognitive impairment.◦Absent permanent ankle joint contractions that prevent passive or active ankle movement.

The exclusion criteria for the participants are the following:

◦Supraspinal lesions or disease.◦Neuropathies of the peripheral nervous system.◦Degenerative neurological disorders of the spine or spinal cord.◦Neoplastic or vascular disorders of the spine or spinal cord.◦Urinary tract infection.◦Presence of pressure sores.◦Permanent ankle joint contractures that prevent passive or active ankle movement.◦Participation in another research study or new rehabilitation program.◦Pregnant women or women who suspect they may be pregnant or may become pregnant.◦People with cochlear implants, pacemaker, implanted infusion device, and/or implanted stimulators of any type.◦People with a history of seizures or medical conditions or medications that increase the possibility of seizures.

### Who will take informed consent? {26a}

Study personnel approved by the Institutional Review Board (IRB) at each study site obtain informed consent according to the principles of the Declaration of Helsinki. All research personnel are trained and certified in policies of privacy, confidentiality, and data integrity.

### Additional consent provisions for collection and use of participant data and biological specimens {26b}

Not applicable. No biological specimens are collected for research purposes. Therefore, no additional consent is obtained from the participants.

## Interventions

### Explanation for the choice of comparators {6b}

There are two active and one sham stimulation interventions delivered to three parallel groups. Active transspinal stimulation is delivered while standing with BWS and/or in the supine position. Sham transspinal stimulation is delivered while standing with BWS. All participants undergo the same locomotor training intervention. The guarantee of locomotor training and the 2:1 ratio of active to sham stimulation reduce the risk of people refusing to participate in the trial. For the sham protocol, the stimulator frequency and waveform is identical to active stimulation, but the intensity is held at the motor threshold for only 1 min, followed by a gradual return to no stimulation for the subsequent 29 min. Studies have suggested that this pattern of stimulation can mimic the initial sensation of stimulation followed by the acclimation to cutaneous stimulation. This approach is expected to improve blinding to active versus sham stimulation.

### Intervention description {11a}

The intervention is 30 min of 30 Hz thoracolumbar transspinal stimulation followed by 30 min of robotic gait training.

#### Transspinal stimulation

While participants are seated, the Thoracic 10 spinous process is identified via palpation and anatomical landmarks. The upper edge of a single cathode electrode (Uni-Patch™, 10.2 cm × 5.1 cm, Wabasha, MA) is placed at the Thoracic 10 spinous process. Two interconnected electrodes (anode; same type as the cathode), are placed on the abdominal muscles or iliac crests, depending on self-reported levels of comfort. These electrodes are connected to a constant current stimulator (DS7A or DS7AH, DS8R, Digitimer Ltd., UK) that is computer-controlled through analog-to-digital data acquisition boards (National Instruments, Austin TX, USA or 1401 plus running Spike 2, Cambridge Electronics Design Ltd., Hertfordshire, England, UK). Transspinal stimulation is initially delivered as a single monophasic pulse of 1 ms. The intensities corresponding to the soleus TEP threshold and maximal amplitudes are noted on the subject’s data sheet. The soleus TEP amplitude is assessed upon paired transspinal stimuli at 60-ms interstimulus interval to establish susceptibility of TEPs to post-activation depression (Fig. 1). When paired transspinal stimulation does not produce TEP depression, the cathodal electrode position is adjusted. Consistent position of the cathodal transspinal electrode during the intervention is ensured by marking the area with a non-allergenic skin pen.

**Fig. 1 Fig1:**
[figure not shown]
Representative transspinal evoked potentials (TEPs) recorded from the knee (vastus lateralis) and ankle (medial gastrocnemius and soleus) muscles in one person with AIS D SCI lying supine upon paired transspinal stimuli at 60-ms interstimulus interval. Note that the TEP depression is larger in ankle muscles compared to TEPs recorded from the knee muscle

Once cathodal positioning, thresholds, and TEP depression upon paired stimuli are confirmed, transspinal tonic stimulation is delivered at a frequency of 30 Hz with a DS8R constant current stimulator (charge-balanced, symmetric, biphasic rectangular pulses of a 1-ms width per phase) for 30 min at 1.2 times the soleus TEP threshold. Stimulation intensity is adjusted based on each subject’s reported discomfort. Transspinal stimulation intensity adjustments are made on a weekly basis based on the TEP threshold.

The different body positions for delivery of transspinal stimulation compare efficacy when (1) ongoing neuronal activity is adjusted continuously (standing vs. supine) and (2) upright posture regulation is needed in the presence or absence of transspinal stimulation (active vs. sham during standing). Upright posture regulation, which is greatly affected after SCI, is one of the key elements of locomotor control [55–60]. During standing, local spinal inhibitory circuits continuously adjust the soleus H-reflex amplitude based on body sway amplitude [61]. The soleus H-reflex amplitude is directly related with postural instability and dynamic balance [62] and is susceptible to cortical control [63, 64]. Specifically, upright balance control requires increased soleus MEPs and decreased soleus H-reflexes [65, 66]. In people with SCI, stand training with transspinal stimulation at varying frequencies (0.2 to 30 Hz) promotes self-assisted standing and upright trunk posture with minimal or absent external assistance [67, 68].

For participants receiving transspinal stimulation while lying supine, hips, and knees are placed in slight flexion and stabilized by holsters and towels to avoid external limb rotations as needed (Fig. 2). For participants receiving active or sham transspinal stimulation while standing, BWS is provided in a standing frame or in the Lokomat to ensure safety (Fig. 2/1a). The initial BWS is adjusted such that knee buckling during standing is absent and decreases over the training course to achieve full body loading. Because prolonged standing may be demanding for individuals with SCI, a 2-min break is given every 10 min of standing.

**Fig. 2 Fig2:**
[figure not shown]
Intervention: Noninvasive transspinal stimulation at 30 Hz for 30 min is delivered during standing (1a) with body weight support as needed to avoid knee buckling and/or while supine with legs semi-flexed at a neutral position (1b) followed by 30 min of locomotor training with the Lokomat 6 Pro (2) within the same training session. In Figs. 1a and 1b the position of the stimulating electrodes is shown

#### Locomotor training

After 30 min of transspinal stimulation all participants receive 30 min of locomotor training with the Lokomat 6 Pro (Hocoma, Switzerland). Over the training course, we use a clinical algorithm to adjust BWS, ankle straps position, and leg guidance force [26]. The tension of the ankle straps is adjusted based on the right and left TA muscle strength evaluated every week. BWS and leg guidance force are adjusted based on presence or absence of knee buckling during standing. BWS, ankle straps position, and leg guidance force are individualized as is the case during outpatient rehabilitation. All intervention and training sessions are supervised by at least two of the authors.

### Criteria for discontinuing or modifying allocated interventions {11b}

Interventions are discontinued when unanticipated or serious adverse events (UAEs, SAEs) result from the intervention and call into question the safety of the intervention or if any new information that becomes available during the trial necessitates stopping the trial. The criteria for halting a training session or an experiment include subject complaints of shortness of breath, light-headedness, confusion, severe headache, or dyspnea; onset of angina; excessive blood pressure (BP) changes (systolic BP greater than 200 mm Hg, diastolic BP greater than 110 mm Hg, systolic BP less than 80 mm Hg); inappropriate bradycardia (drop in heart rate (HR) greater than 15 beats per min); increased HR exceeding 80% of the predicted maximum HR (HRmax = 220 − age); or participant reports a Borg perceived exertion rate of greater than 15. Should the session be halted, the participant will be asked to rest while BP and HR are monitored and will resume only when BP and HR return to baseline values. If any of these conditions persist after rest, the participant’s primary physician will be contacted, and the participant is referred for evaluation. If the participant complains of angina at rest, loss of consciousness occurs, or cardiac arrest, 911 will be called immediately. There are no special criteria for modifying allocated interventions.

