### Plans to promote participant retention and complete follow-up {18b}

Explanation of the study, including possible benefits, increases recruitment and retention in randomized clinical trials [92]. It is a standard procedure in our lab to describe the research study in detail and answer all questions that a participant may have. The eligible participant is always encouraged to ask questions about the procedures and no information is withheld. During the discussion, participants are informed of the expectation that they can commit to traveling to either site for training/intervention sessions at least 4 times per week for up to 3 months. If the participant or study team perceives difficulty in meeting these expectations, then enrollment is deferred. After the consent form is signed, we develop a calendar for each participant based on the time needed to come to the lab, job obligations, or other commitments. The calendar includes all experimental and training sessions for the total duration of the study and is emailed to the participant. We also make use of electronic calendar invitations for reminders, and emails or texts before each visit depending on the participant. These procedures can decrease some common reasons for dropouts in clinical trials such as fear and anxiety during the study, schedule conflicts, forgetting visits, lack of appreciation, and misunderstood expectations. Thus, the procedures that we follow — explaining the importance of participation, setting expectations, reminders of visits, accommodation of the schedule, and promptly responding to inquiries — are expected to contribute to better retention of participants.

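### The session-halting rule requires no medical evaluation for new angina that settles with rest, and lets the session resume on blood pressure and heart rate alone

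*Protocol article*

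**What the plan says.** The protocol article, under Criteria for discontinuing or modifying allocated interventions {11b}, sets out what happens when a training session or experiment has to stop. The halting list mixes symptoms with vital-sign limits, and "onset of angina" is one of the symptoms. After any halt the participant rests under blood pressure (BP) and heart rate (HR) monitoring and "will resume only when BP and HR return to baseline values".

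Two escalation steps follow. Contact with the primary physician and referral begin with the condition "If any of these conditions persist after rest". The emergency call begins with "If the participant complains of angina at rest" and also covers loss of consciousness and cardiac arrest.

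The same section opens with a rule for stopping the intervention when unanticipated or serious events "result from the intervention and call into question the safety of the intervention", or when new information requires the trial to stop. It closes with "There are no special criteria for modifying allocated interventions".

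The Eligibility criteria {10} require "Stable medical condition without cardiopulmonary disease or cognitive impairment" and admit people up to age 70.

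**The concern.** Several halting triggers are symptoms, but the stated test for resuming looks only at BP and HR. For most of those symptoms the referral step is a reasonable backstop, because a symptom that does not clear sends the participant to a physician. Angina differs in that exertional angina typically does clear with rest, so a rule that escalates only on persistence can miss the usual presentation.

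Because cardiopulmonary disease is not allowed at entry, angina during a session would be a new finding and would put continued eligibility in doubt. At stake is whether a participant with possible new coronary disease can be put back into standing or robotic gait training on the same day without medical evaluation.

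**Working it through.** No figure in the plan bears on this rule, so the check is to follow one case through it. The case is angina that starts during a session and resolves fully with rest, with BP and HR back at baseline.

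| Step in {11b} | Stated condition | Met in this case? |
|---|---|---|
| Halt | "onset of angina" | Yes |
| Rest with monitoring | Follows any halt | Yes |
| Physician contact and referral | "If any of these conditions persist after rest" | No, it has resolved |
| Emergency call | Angina at rest, loss of consciousness or arrest | No |
| Resume | BP and HR at baseline | Yes |

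The session may therefore resume with no evaluation.

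I then looked for other text that would close the gap.

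- **Opening rule of {11b}.** It requires a judgement that the event came from the intervention and puts its safety in question. It sets no evaluation step for an individual.
- **Close of {11b}.** It states that there are no special modification criteria.
- **Locomotor training, under Intervention description {11a}.** At least two of the authors supervise each session. Nothing says that either gives medical clearance.
- **Strategies to improve adherence {11c}.** Staff hold written intervention protocols. They are described in terms of delivery and fidelity, not clearance after a symptom.
- **Data monitoring committee {21a}.** Its role concerns stopping rules and event determination, not clearing an individual to resume.
- **Adverse event reporting {22} and auditing {23}.** Events are recorded and reported to the principal investigators, who are responsible for safety daily. Neither section makes evaluation a condition of resuming.

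The cost of a stricter rule uses these inputs: 40 sessions and 45 participants (Abstract), 20% projected dropout (Sample size {14}), and attendance "at least 4 times per week for up to 3 months" (Plans to promote participant retention {18b}).

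- One lost session: 1/40 = 2.5% of that participant's course.
- One participant not cleared: 1/45 = 2.2% of the sample. The projected dropout allows 45 × 0.20 = 9.
- Course length at exactly 4 sessions per week: 40/4 = 10 weeks. More sessions per week make it shorter.
- Time available: 3 months is about 13 weeks, so 13 − 10 = about 3 weeks or more remain for sessions delayed while clearance is sought.

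**The case against.** The best defence is that returning to baseline is a necessary condition for resuming and is never called sufficient. Staff may decline to resume, and a competent team probably would. This is a condensed article, and the full protocol or the staff procedures may contain a clearance step.

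The uncovered case is also narrow. Angina that continues into the rest period triggers referral and arguably the emergency call. Angina during supine stimulation is already angina at rest. Sessions also halt when HR exceeds 80% of the predicted maximum or the Borg rating exceeds 15, and entry excludes cardiopulmonary disease.

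Much of this stands, and it limits the point. It does not remove it, because {11b} is not merely brief: it sets out the whole sequence from halt to emergency call and, within that sequence, fixes a purely haemodynamic test for resuming.

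Three stronger readings are tempting and are not supported:

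- **That the rule orders resumption.** It does not; it only permits it.
- **That it authorises all later sessions without evaluation.** The section says nothing about later sessions, and that silence is not permission.
- **That such an event would go unnoticed until the annual review.** Annual submission applies only to ordinary adverse events. Serious, serious unexpected and unanticipated events have prompt routes, and angina is not among the robotic-training events listed in {22}, so it could well be classed as unanticipated. The principal investigators also receive event reports and hold daily safety responsibility, and each site meets at least weekly.

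**Conclusion.** The point holds in limited form. As written, {11b} triggers no medical evaluation for new angina that settles with rest and permits same-day resumption once BP and HR are at baseline. Oversight and reporting provisions elsewhere may bring the event to the investigators' attention, but none requires evaluation before the session restarts.

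The documents give no rate of angina in this setting, so I make no estimate of the number affected. The potential harm to one participant is serious and the probability is unknown, so the severity is minor to moderate. Nothing in the sample size, allocation, outcomes or analysis is affected. The conclusion assumes that no undisclosed procedure adds a clearance step; if one exists, the published rule should state it.

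**What to change.** Amend {11b} in two places, covering both training sessions and experiments:

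1. A session resumes only when the symptom that caused the halt has resolved and BP and HR are at baseline.
2. Any new-onset angina, even if it settles with rest, ends that session and triggers the physician contact and referral already described there, with medical clearance required before the next session.

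No new referral pathway is needed. The usual cost is one lost or delayed session, which the spare weeks in the schedule can normally absorb. In rare cases a participant will not be cleared, and the projected dropout has room for that. The amendment can follow the route in {25}. Under Trial status, recruitment runs to about April 2025, so it would protect anyone still to be trained when it takes effect.

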### Strategies to improve adherence to interventions {11c}

To maintain intervention fidelity, we developed and provided to staff members intervention protocols that detail the procedures for conducting the thoracolumbar transspinal stimulation and the locomotor training. To assure the correct implementation of the protocols, we trained staff members to become familiar with the theory and scientific literature supporting the intervention and with the laboratory equipment. We assess the fidelity with which the locomotor training is implemented in terms of compliance with the protocol and adherence to the procedure by recording for every session a participant received, the adjustments of a) BWS, b) leg guidance force, c) treadmill speed and by monitoring continuously participants’ engagement and performance using real-time biofeedback. Additionally, records of the thoracolumbar transspinal stimulation delivered are kept by staff members for each participant. Date, duration, and intensity of stimulation are recorded for every session, while the TEP threshold is established and recorded on a weekly basis. The position of the cathodal stimulation electrode is marked at the first session and checked in every session to ensure that electrode configuration remains the same.

### Relevant concomitant care permitted or prohibited during the trial {11d}

During the trial, enrolled participants are not permitted to participate in another clinical trial and are encouraged to continue their daily routine as before enrollment and participation. We frequently remind participants of the expectations to not initiate other rehabilitation programs during their participation in this study and to keep us informed of any changes in their clinical medication schedules.

### Provisions for post-trial care {30}

Not applicable. All participants benefit from the multiple sessions of locomotor training. There is no increased risk in any of the randomized groups.

### Outcomes {12}

#### Primary outcomes

The primary outcomes are neurophysiological biomarkers that accurately probe corticospinal and spinal neuroplasticity (at presynaptic and postsynaptic motoneuron levels):Corticospinal neuronal excitability:

We establish the active MEP threshold that corresponds to the intensity that evokes 10 responses of at least 50 mV following 20 1-ms transcranial magnetic stimulation (TMS) pulses in seated subjects. Then, the soleus MEP recruitment input–output curve is assembled while maintaining small-amplitude contractions. During BWS-assisted stepping, MEPs are recorded at 1.3 times the right soleus MEP active threshold randomly at different phases of the step cycle (divided into 16 equal bins or time windows) based on the signal from the right foot switch. During stepping, MEPs are collected before and after intervention using Lokomat settings matched to the baseline, while an effort is made to record MEPs using Lokomat settings matched to those of the last training session. This establishes changes at matched settings and adaptations during more demanding stepping conditions. MEPs recorded at different stimulation intensities (recruitment curve) are measured as peak-to-peak amplitude and normalized to the soleus maximal M-wave (Mmax) evoked by posterior tibial nerve stimulation to counteract differences in muscle fiber composition across subjects. Stimulation intensities are normalized to the intensity corresponding to the 50% of the MEPmax amplitude, estimated based on the sigmoid function fit to the data. For the participants who have obtainable soleus MEPs at baseline, the main outcomes from this experiment are the MEPmax from the MEP recruitment curves and the MEP amplitude at the mid-stance and mid-swing phases before and after the intervention.2)Spinal neuronal excitability:*2a) Soleus H-reflex rate-dependent (or homosynaptic) depression*: To assess restoration of homosynaptic depression exerted at the synapses between muscle spindle primary Ia afferents and alpha motoneurons, soleus H-reflexes following posterior tibial nerve stimulation at the popliteal fossa with a 1-ms pulse are recorded from seated subjects at different frequencies (1.0, 0.33, 0.2, 0.125, and 0.1 Hz). Homosynaptic depression is greatest at 1.0 Hz and fully recovers at 0.125 and 0.1 Hz [69]. Homosynaptic depression cannot be recorded during stepping because it is abolished by strong spinal inhibitory circuits and efferent activity. The main outcome measure from this neurophysiological biomarker is the soleus H-reflex 1.0/0.1 Hz ratio [70].*2b) Soleus H-reflex depression by antagonistic nerve stimulation*: To examine the restoration of reciprocal inhibitory actions on antagonistic alpha motoneurons, the soleus H-reflex is conditioned by common peroneal nerve (CPN) stimulation at conditioning-test (C-T) intervals of 0, 1, 2, 3 and 4 ms, with subjects seated [71–75]. Reproducible CPN conditioning stimulation is ensured by using a stable, small-amplitude TA M-wave and similar soleus M-wave amplitudes under control and conditioning stimulations. Soleus H-reflexes are measured as peak-to-peak amplitude, accepted for M-waves ranging from 2 to 8% of the maximal M-wave (Mmax), and normalized to the Mmax. The main outcome is the amplitude of the conditioned soleus H-reflex as a percentage of the control H-reflex. The C-T interval for which reciprocal inhibition is present or reciprocal facilitation is the smallest is further investigated during BWS-assisted stepping. The main outcomes are the conditioned H-reflex at rest and during the stance and swing phases of BWS-assisted stepping, which both reflect the amount of reciprocal inhibition.*2c) Control and conditioned soleus H-reflexes during stepping*: During standing with BWS as needed, the soleus H-reflex and M-wave recruitment curves are assembled. Then, each participant steps with the assistance of the Lokomat, and soleus H-reflexes are recorded under control conditions and following CPN conditioning stimulation randomly across 16 equal time bins into which each step cycle is divided based on the signal from the foot switch [75]. The tibial nerve stimulation intensity is adjusted in real-time online to evoke H-reflexes such that their corresponding M-waves are 2–8% of the Mmax evoked 80 ms after the test H-reflex at each bin (Fig. 3). Control and conditioned soleus H-reflexes during stepping are collected before (baseline) and 1–2 days after completion of all 40 intervention sessions at Lokomat settings matched to baseline and the last training session. This approach determines changes at matched settings and reflex adaptation at more demanding settings [76]. During stepping, soleus H-reflexes are measured as peak-to-peak amplitude, accepted for M-waves ranging from 2 to 8% of the Mmax, normalized to the Mmax, and averaged for each bin of the step cycle. The main outcome is the control and conditioned soleus H-reflex amplitude normalized to the Mmax at mid-stance and mid-swing phases.
